### Data management

Data sources will be the patient’s medical record and any other medical record of clinical findings accrued as part of routine care; retrospective data may be obtained from the patient’s medical record. All data related to the study will be entered in the eCRF, housed on IBM Clinical Development, and will be checked for accuracy and completeness as a component of ongoing study monitoring by an independent contract research organization (CRO) designated by Chiesi Farmaceutici S.p.A. Access to the eCRF will be granted to authorized personnel; sites will only be able to access data of patients enrolled at their site and the CRO will be entitled to access all data in a read-only mode.

For patients who discontinue the study, all efforts will be made to complete and report the observations as thoroughly as possible. If a patient is transferred to another continuing care site, the new treating site will be formally involved in the study after a request of authorization submitted to the relevant ethics committee and regulatory authority. In case of withdrawal, the investigator must report the main reason for withdrawal.

### Study size

As this is an observational study and there is no formal hypothesis testing, the size of the study was conceptualized based on assumed different proportions of GTR in treatment-naïve patients who can perform functional tests after 3 years of treatment. Assuming at least 70 treated patients are enrolled, and assuming a GTR of at least 0.60, the lower limit of the two-sided 95% confidence interval (Clopper–Pearson) is always above 45.0% (Table 4), which is considered a clinically relevant response. Thus, the efficacy analysis is based on a hypothetical treated population of at least 70 patients.

**Table 4 Tab4:** Efficacy analysis based on hypothetical treated population of at least 70 patients

Expected proportion	95% CI lower limit	95% CI upper limit	95% actual width
0.60	0.476	0.715	0.239
0.65	0.527	0.760	0.234
0.70	0.579	0.804	0.225
0.75	0.632	0.846	0.214
0.80	0.687	0.886	0.199

*CI* confidence interval

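### The study-size statement that the lower confidence limit is always above 45% holds only for an observed GTR of at least 0.60 among 70 evaluable patients, not for an assumed true rate among 70 enrolled

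*Protocol article*

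**What the plan says.** The Study size section of the protocol article states that "there is no formal hypothesis testing" and sizes the registry by the precision of the GTR proportion. The population for that proportion is treatment-naïve patients "who can perform functional tests after 3 years of treatment". The calculation then rests on two conditions: "Assuming at least 70 treated patients are enrolled" and "assuming a GTR of at least 0.60". Under these, the lower limit of the two-sided 95% Clopper–Pearson interval "is always above 45.0% (Table 4), which is considered a clinically relevant response". The section concludes that the efficacy analysis is based on a hypothetical treated population of at least 70.

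Table 4 lists the interval for proportions from 0.60 to 0.80 in a column headed "Expected proportion". Its first row gives 0.476 to 0.715.

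Three other places bear on the denominator:
- Effectiveness variables restricts GTR to patients naïve to velmanase alfa who can do the functional tests, assessed after 3 years of treatment.
- Study design says that the registry imposes no mandatory assessments.
- Footnote g of Table 2 says that assessments are recorded only where routine care provides them.

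**The concern.** Two features of the statement go beyond what Table 4 supports.

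First, the 0.60 is described as assumed and expected, which is planning language for an underlying rate. Table 4 instead shows the interval that results when the observed proportion equals the listed value exactly. If the true rate is 0.60, the observed count varies around 42 of 70, and some of the plausible counts give a lower limit below 45%. The word *always* leaves no room for that variation.

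Second, the section describes one population (naïve, able to do the tests, at 3 years) and counts another (treated patients enrolled). Table 4 uses all 70 as the denominator.

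This is the article's only justification of the study size. It concerns the primary effectiveness outcome of a post-approval commitment, and 45% is the section's own benchmark for clinical relevance. A reader could take from it an assurance that the design does not have.

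**Working it through.** **Inputs.** From Study size and Table 4: n = 70, two-sided 95% Clopper–Pearson interval, proportions 0.60 to 0.80, benchmark 0.45. The article gives no proportion of non-evaluable patients, so the smaller n used in steps 4 and 5 are assumptions.

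**Formulas.** For x responders out of n:
- lower limit = 2.5% quantile of Beta(x, n − x + 1)
- upper limit = 97.5% quantile of Beta(x + 1, n − x)
- probability of clearing the benchmark = P(X ≥ c), with X binomial(n, p) and c the smallest count whose lower limit exceeds 0.45

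**Step 1: reproduce Table 4.** With x = 70p:

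| p | x | Lower | Upper |
|---|---|---|---|
| 0.60 | 42 | 0.476 | 0.715 |
| 0.65 | 45.5 | 0.527 | 0.760 |
| 0.70 | 49 | 0.579 | 0.804 |
| 0.75 | 52.5 | 0.632 | 0.846 |
| 0.80 | 56 | 0.687 | 0.886 |

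All five rows agree with the article to three decimals. A minor remark: the 0.65 and 0.75 rows rest on 45.5 and 52.5 responders, which cannot be observed.

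**Step 2: find the threshold at n = 70.** 40/70 gives a lower limit of 0.4475 and 41/70 gives 0.4617. So c = 41, an observed proportion of 41/70 = 0.586.

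**Step 3: probability of reaching the threshold if the listed value is the true rate (n = 70).**

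| True GTR | P(X ≥ 41) |
|---|---|
| 0.60 | 0.645 |
| 0.65 | 0.894 |
| 0.70 | 0.985 |
| 0.75 | 0.999 |
| 0.80 | about 1.000 |

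At a true rate of 0.60 the limit fails to clear 45% with probability 1 − 0.645 = 0.355.

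**Step 4: the same probability with fewer evaluable patients (assumed numbers).**

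| Evaluable n | Share of 70 | c | At true 0.60 | At true 0.65 | At true 0.70 |
|---|---|---|---|---|---|
| 63 | 90% | 37 | 0.634 | 0.879 | 0.979 |
| 56 | 80% | 34 | 0.515 | 0.793 | 0.949 |
| 49 | 70% | 30 | 0.492 | 0.761 | 0.930 |
| 42 | 60% | 26 | 0.467 | 0.723 | 0.903 |

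**Step 5: how far the denominator can shrink if 0.60 is the observed proportion.** Take the smallest whole number of responders that makes the observed GTR at least 0.60, and reduce n from 70. The lower limit stays above 0.45 down to n = 46 (28/46 gives 0.4537). It first fails at n = 45, where 27/45 = 0.600 gives 0.443. That is 70 − 45 = 25 patients lost, or 25/70 = 36%. Because counts are whole numbers, the pattern below 45 is not smooth: 27/44 = 0.614 gives 0.455, which clears the benchmark again.

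**The case against.** The strongest reply is that this is sizing by precision, with no test declared. In such tables the listed proportion is normally the value at which the interval is evaluated, and *always* can be read as meaning in every row of Table 4. Read so, the statement is correct. This stands: a reader might infer that the sentence is simply false or that Table 4 is miscalculated, and neither is supported.

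A second reply is that the 65% is the least favourable case. The text says at least 0.60, and the Background reports response in 13 of 15 treated patients (86.7%) in the pivotal trial and 29 of 33 (87.9%) in the integrated data, with 71% among adults. At 0.70 the probability with 70 evaluable patients is already 98.5%, and at 0.87 it is 0.9997 even with 35. This also stands. It would be wrong to present 65% as the registry's likely chance of clearing 45%.

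A third is that no decision depends on clearing 45%, so the probabilities resemble power for a test that the plan does not make. This is right in that no assurance target can be imposed, and the figures do not show that the registry is too small. It does not rescue the wording, because the section itself names the benchmark and derives the 70 from it.

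On the denominator, 70 is a minimum, recruitment is indefinite, and an attrition allowance may be in the full protocol. A reader might infer that the evaluable number will fall well short of 70. The article gives no rate, so that cannot be shown. What remains is that the section ties the proportion to one population and gives the count for another.

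**Conclusion.** The point holds in a limited form. The 45% statement is true for an observed GTR of at least 0.60 among 70 evaluable patients. It is not true as a guarantee for an assumed or expected GTR of 0.60: there, 41 or more responders out of 70 are needed, with probability about 65%. The shortfall is confined to the bottom of the stated range, since the probability is 89% at 0.65, 98.5% at 0.70 and over 99% from 0.75. These figures assume independent responses and a full 70 evaluable patients.

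The enrolled-versus-evaluable mismatch applies on either reading. At the same observed proportion, fewer than 70 evaluable patients give wider intervals than Table 4 shows. On the observed reading the 45% statement itself is safe down to 46 evaluable patients and can first fail at 45. Whether the registry will come near that number cannot be determined from the article.

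Severity is moderate. No analysis and no patient number is shown to be wrong; the only stated justification of the study size promises more than it delivers and attaches it to the wrong count.

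**What to change.** In Study size and Table 4:

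1. Say that Table 4 gives the interval for an *observed* GTR among 70 treatment-naïve patients evaluable at 3 years, and relabel the proportion column to match.
2. Delete *always* and replace the sentence with, for example: *With 70 treatment-naïve patients evaluable for GTR at 3 years, the lower 95% Clopper–Pearson limit exceeds 45% if at least 41 respond; the probability of this is about 65%, 89% and 98.5% for a true GTR of 0.60, 0.65 and 0.70.*
3. Either define 70 as the number evaluable for GTR, or keep 70 as enrolled and add rows to Table 4 for smaller evaluable numbers, marked as assumptions (for example 63, 56, 49 and 42). Using whole responder counts would also remove the 45.5 and 52.5 in the present rows.

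The cost is an edit to one paragraph and one table, and a stated figure that looks less favourable than the present one. Restating the precision requires no extra patients. If 70 is defined as the evaluable number, enrolment would have to exceed 70 by whatever share proves non-evaluable, which the indefinite recruitment period allows.

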### Statistical analyses

Baseline demographic and disease characteristics will be presented by means of descriptive statistics and frequency distributions, as appropriate. Descriptive safety outcomes will be presented and summarized over time. For AEs, both the frequency of patients with an AE and the number of events will be presented by year from baseline. Safety variables will be presented based on person-years at risk. Effectiveness variables will be summarized by means of descriptive statistics or frequency of distribution, as appropriate, and all variables (actual values and change from baseline, if applicable) will be presented by time point. The effects of baseline characteristics on effectiveness will be evaluated by means of regression/logistic models. Covariates in the model will be age (< 18 and ≥ 18 years), sex (male, female), sibships, genotype (Groups 1, 2, and 3, per Borgwardt et al.) [18], residual enzymatic activity (< 10, 10 to < 15, and ≥ 15 nmol/h/mg), and Childhood Health Assessment Questionnaire Disability Index (0–1, 1–2, and 2–3).

Provided that a sufficient number of nontreated patients with adequate data are enrolled, a comparison will be conducted between the velmanase alfa-treated and nontreated groups. Propensity score (PS) analysis will be used to compare GTRs after 3 years; the PS will be calculated as the predicted probability of response using logistic regression, with the same covariates as used for the baseline characteristics regression. Subgroup analyses may be performed depending on overall sample size; results will be presented descriptively.

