### Effectiveness variables

Efficacy outcomes to be assessed during routine clinical care are shown in Table 1. For patients under 4 years of age, a 3-min stair climb test (3MSCT) and 2-min walk test (2MWT) are suggested. The forced vital capacity (% volume predicted) is suggested for patients over 4 years of age, and according to the judgment of the treating physician. The proposed schedule of assessments is shown in Table 2, but, again, assessments will be made based on the participating centers’ Standard Operating Procedures.

A global treatment response (GTR) to velmanase alfa will be evaluated in velmanase alfa-naïve patients able to perform the functional tests after 3 years of treatment. The GTR will assess patients in three clinical domains (pharmacodynamic, functional, and QoL) consisting of 1 or > 1 endpoint (Table 3). The pharmacodynamic domain comprises a measure of the accumulated substrate in alpha-mannosidase deficiency, the main pathogenic factor for disease manifestations; a decrease in oligosaccharides is a key biomarker of the pharmacologic effect of the ERT [4]. The second domain includes pulmonary function, endurance, and fine and gross motor proficiency, i.e., all the functional endpoints of the disease [4]. The QoL domain relates to patient-related outcomes of disease burden, disability, and pain [4]. A global response is defined as improvements exceeding the established minimal clinical important difference (MCID) (Table 3) in ≥ 1 endpoint in ≥ 2 of the domains [4]. The MCIDs are derived on the basis of those used in clinical conditions with the highest similarity to alpha-mannosidosis (proxy diseases) [14–17]. Collection of the same effectiveness variables is suggested for patients who are not treated with velmanase alfa, in order to support the description of the natural course of the disease.

**Table 3 Tab3:** Clinical domains, endpoints, and MCID thresholds for the GTR

Domain	Endpoint	Established MCID^a^
Pharmacodynamic	Serum oligosaccharides	Last serum oligosaccharide value ≤ 4 µmol/L
Functional	3MSCT	Improvement ≥ 7 steps/min [14]
	6MWT	Improvement ≥ 30 m [16]
	FVC%	Improvement ≥ 10% [15]
Quality of life	CHAQ DI	Improvement ≤ –0.130 [17]
	CHAQ Pain VAS	Improvement ≤ –0.246 [17]

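### Baseline CHAQ-DI band is evaluated as an influence on effectiveness while CHAQ-DI change is part of the GTR, so regression to the mean makes more disabled patients look like better responders

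*Protocol article*

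**What the plan says.** Statistical analyses (protocol article): "The effects of baseline characteristics on effectiveness will be evaluated by means of regression/logistic models". One of the listed covariates is "Childhood Health Assessment Questionnaire Disability Index (0–1, 1–2, and 2–3". The influence of baseline disability is thus a quantity to be estimated and reported, not only a nuisance term.

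Effectiveness variables, Table 3: the quality-of-life domain of the GTR has two endpoints, CHAQ-DI and CHAQ Pain VAS. The CHAQ-DI criterion is "Improvement ≤ –0.130 [17", which is a change from baseline. A global response needs improvement "in ≥ 1 endpoint in ≥ 2 of the domains [4", and there are three domains. The abstract names the GTR as the primary effectiveness outcome.

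Study size: "As this is an observational study and there is no formal hypothesis testing". Table 4 plans for expected GTR proportions of 0.60 to 0.80 in 70 treated patients.

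The baseline-characteristics regression is described without a treatment term. The comparison with untreated patients is a separate analysis and depends on enough of them being enrolled.

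**The concern.** The baseline CHAQ-DI score enters the model twice. It defines the band, and it is subtracted from the follow-up score to decide whether the CHAQ-DI criterion is met. A patient placed in a high band partly through measurement error tends to score lower next time, and a patient placed in a low band tends to score higher. A patient with a baseline below 0.130 cannot meet the criterion, because the scale stops at 0. Both mechanisms push the same way: greater baseline disability looks like better response.

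At stake is how one coefficient is read. The Discussion says the registry will collect data on disease modifiers and that registries of this kind support treatment strategies. A report that more disabled patients respond better could enter that discussion although it arose only from the arithmetic of the change score.

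**Working it through.** **1. The plan's own figures.** Clopper–Pearson limits for n = 70 reproduce Table 4 to three decimals (for example 0.476 to 0.715 at 0.60, and 0.687 to 0.886 at 0.80). They are not in dispute. Here they only supply the planning range for the GTR.

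**2. Why the direction is fixed.** Let baseline B = T + e1 and follow-up F = T + e2, with no true change and independent errors of variance σe². Then cov(F – B, B) = –σe², so the slope of change on baseline is –σe²/(σT² + σe²), which is negative whenever there is any measurement error. With assumed σT = 0.7 and σe = 0.25, it is –0.0625/(0.49 + 0.0625) = –0.113 per CHAQ-DI point.

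**3. CHAQ-DI response by band, no true change.** Assumptions, none of them from the article: true CHAQ-DI normal with mean 1.4 and SD 0.7; independent normal errors at both visits; all values limited to 0–3; bands cut at 1 and 2. Response means change ≤ –0.130 (Table 3). Simulated with 4 million patients per setting.

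**4. GTR by band.** Assumed pharmacodynamic response 0.80, functional 0.60 and Pain VAS 0.30, all independent of CHAQ-DI. With CHAQ-DI response r in a band:

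- both other domains met: 0.80 × 0.60 = 0.48
- exactly one met: 0.80 × 0.40 + 0.20 × 0.60 = 0.44
- quality-of-life domain met: 1 – 0.70 × (1 – r) = 0.30 + 0.70r
- GTR = 0.48 + 0.44 × (0.30 + 0.70r) = 0.612 + 0.308r

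| Within-patient SD | CHAQ-DI response, bands 0–1 / 1–2 / 2–3 (%) | Top minus bottom | GTR by band (%) | Top minus bottom | Overall GTR (%) |
|---|---|---|---|---|---|
| 0.10 | 13.6 / 18.1 / 20.8 | 7.2 | 65.4 / 66.8 / 67.6 | 2.2 | 66.6 |
| 0.15 | 19.8 / 27.3 / 33.0 | 13.2 | 67.3 / 69.6 / 71.4 | 4.1 | 69.3 |
| 0.25 | 23.7 / 36.4 / 46.9 | 23.2 | 68.5 / 72.4 / 75.6 | 7.1 | 71.9 |
| 0.35 | 23.7 / 40.6 / 55.1 | 31.4 | 68.5 / 73.7 / 78.2 | 9.7 | 73.1 |

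Overall GTR lies within the planning range in every row.

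**5. Sensitivity.** The GTR spread equals the CHAQ-DI spread times (probability that exactly one other domain is met) × (1 – pain response), here 0.44 × 0.70 = 0.308. It therefore moves with the assumed rates.

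- Baseline mean 1.0 instead of 1.4: GTR spread 2.8, 4.8, 8.2 and 10.8 points for the four SDs.
- Pharmacodynamic 0.90, functional 0.70, pain 0.30, mean 1.4: 1.7, 3.1, 5.5 and 7.5 points.
- A separate simulation with observed SD 0.65, mean 1.0, reliability 0.80 (error SD 0.65 × √0.20 = 0.29), pharmacodynamic 0.80, functional 0.50, pain 0.20: CHAQ-DI response 25%, 45% and 62%; GTR 60%, 68% and 75%, a spread of 15 points.

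**6. Share due to the floor.** In that last setting the odds ratio for CHAQ-DI response, top versus bottom band, is 4.3 without limiting scores to 0–3 and 5.0 with it. Regression to the mean does most of the work.

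**The case against.** - **No test is planned.** This is correct. A reader might infer an inflated false-positive rate, but the article sets no significance level or decision rule for these coefficients. What remains is bias in an estimate, which misleads with or without a p-value.
- **The article does not say that CHAQ-DI change is regressed on CHAQ-DI band.** Also correct. The wording "all variables (actual values and change from baseline, if applicable) will be presented by time point" concerns descriptive presentation. The CHAQ-DI figures above apply only if that outcome is modelled. The GTR is the primary effectiveness outcome, and the propensity-score paragraph links it to the same covariates, so the GTR figures are the ones to weigh.
- **The GTR dilutes the effect.** It does. Leaving out Pain VAS and setting functional response at 40% gives 45%, 52% and 58% by band at SD 0.25, but Table 3 includes Pain VAS, and the overall GTR of about 52% then falls below the planning range.
- **Adjusting for a baseline value is good practice.** Yes, as adjustment. The difficulty is reporting its coefficient as an effect on effectiveness. Modelling the follow-up score on baseline would not cure the GTR, whose CHAQ-DI criterion is change-based.
- **The floor is a real feature of the criterion.** Granted: a patient below 0.130 truly cannot meet it. That says nothing about whether the drug works less well in that patient.
- **Details belong in the analysis plan.** The point rests on two choices the article does fix, the covariate list and the GTR definition.

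A reader might also infer that the age and genotype coefficients are biased. Nothing in the article gives their correlation with CHAQ-DI, and no calculation supports the claim.

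**Conclusion.** The point holds for models whose outcome contains CHAQ-DI change, which includes the GTR. The artefact always favours the more disabled bands; a true effect of baseline disability could add to it or offset it. Under the main assumptions, for within-patient SDs of 0.15 to 0.35, the spread between top and bottom bands is about 13 to 31 points for CHAQ-DI response and about 4 to 10 points for the GTR, falling to about 2 points for the GTR at SD 0.10. These are not bounds: one alternative set of assumptions gives 15 points for the GTR. All sizes rest on assumed reliability, distribution and domain response rates, and on no true individual change over the three years.

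Models for oligosaccharides, 3MSCT, 6MWT or FVC% are not coupled in this way. The article does not itself claim that more disabled patients benefit more, and this point does not call the overall GTR proportion into question.

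**What to change.** 1. Keep baseline CHAQ-DI as an adjustment covariate, but state that its coefficient will not be interpreted as an effect on effectiveness in any model whose outcome includes CHAQ-DI change or response.
2. For the GTR, add one model in which the CHAQ-DI endpoint is removed from the response. Keep the pharmacodynamic and functional domains, let Pain VAS alone represent quality of life, and keep the two-domain rule. Read the baseline CHAQ-DI effect from that model.
3. In the treated-only models, label the coefficients as prognostic, not as modification of the velmanase alfa effect.

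The cost is some wording and one extra model on data already collected. The reduced response has somewhat fewer responders: under the main assumptions 0.48 + 0.44 × 0.30 = 61.2%, against 66.6% to 73.1% for the full GTR. The change removes the direct reuse of the CHAQ-DI score. If same-visit errors in CHAQ-DI and Pain VAS are correlated, a smaller residue could remain.

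### Age enters the response and propensity models only as under or over 18, which discards information if its effect is graded, and the CHAQ-DI bands overlap at 1 and 2

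*Protocol article*

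**What the plan says.** The Statistical analyses section plans a search for baseline predictors: "The effects of baseline characteristics on effectiveness will be evaluated by means of regression/logistic models". It then lists the covariates and prints their coding: "Covariates in the model will be age (< 18 and ≥ 18 years), sex (male, female), sibships", genotype in three groups, "residual enzymatic activity (< 10, 10 to < 15, and ≥ 15 nmol/h/mg") and "Childhood Health Assessment Questionnaire Disability Index (0–1, 1–2, and 2–3"). If enough untreated patients with adequate data are enrolled, treated and untreated patients will be compared on global treatment response (GTR) after 3 years by a propensity score built "with the same covariates as used for the baseline characteristics regression". The age split at 18 therefore applies in both places.

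Two parts of the Background bear on age. It describes the disease as a continuum that progresses slowly and at varying rates, with ataxia appearing in the third decade of life. It also reports that, in the integrated data of the development programme, all pediatric patients but only 71% of adults were global responders.

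**The concern.** Age is the covariate for which the article itself reports a difference in response, yet it has the coarsest coding of the three measured on a continuous scale: two levels, against three for enzyme activity and CHAQ-DI. A patient just above the functional-test age and a 17-year-old are treated as the same. An 18-year-old and a much older adult are also treated as the same. If response falls gradually with age, the split weakens the predictor analysis. In a treated-untreated comparison, age differences inside each band would go unadjusted and would be read as part of the treatment effect.

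The CHAQ-DI bands raise a simpler problem. As written, a score of exactly 1 or 2 cannot be assigned to a single band. The enzyme-activity bands in the same sentence are written without overlap, so the difference looks like a slip, but it is in the text that defines the model.

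**Working it through.** **1. The plan's own calculation.** The only design calculation is Table 4 in Study size: "Assuming at least 70 treated patients are enrolled, and assuming a GTR of at least 0.60", for which "the lower limit of the two-sided 95% confidence interval (Clopper–Pearson) is always above 45.0"%. With x = 70p responders, the Clopper–Pearson limits are the 0.025 quantile of Beta(x, 70 − x + 1) and the 0.975 quantile of Beta(x + 1, 70 − x). At p = 0.60, x = 42, giving 0.476 and 0.715. The other rows also reproduce to three decimals. The plan states no figure for the covariate models, so n = 70 is the only input taken from here.

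**2. Prior evidence on age.** The Background gives 29 responders among 33: 19 pediatric and 10 adult. If all 19 children responded, 33 − 19 = 14 were adults, and 10/14 = 71%. This shows a difference between children and adults. It does not show whether the difference is a slope or a step.

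**3. Information kept by the bands.** The share kept is the variance of the band means divided by the total variance. The documents give no covariate distributions, so ranges over several assumed ones are shown.

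| Covariate | Share kept | Share lost |
|---|---|---|
| Age, 2 bands | 0.47–0.73 | 27–53% |
| Residual enzyme activity, 3 bands | 0.81–0.84 | 16–19% |
| CHAQ-DI, 3 bands | 0.82–0.89 | 11–18% |

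Only age loses a large share.

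**4. Power for a graded age effect.** Simulated with n = 70 and a two-sided 5% likelihood-ratio test on 1 df. Age is uniform from 4 to 28 or 38 years, and response is logit-linear in age with the slope set to give the stated rates in children and adults.

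| GTR, children vs adults | Age < 18 / ≥ 18 | Age continuous |
|---|---|---|
| 0.85 vs 0.65 | 48–50% | 62–65% |
| 0.75 vs 0.50 | 58–60% | 72–73% |

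With age uniform from 4 to 40, 70% response at the mean age and odds ratios per SD of 0.67, 0.50 and 0.40, power is 25%, 58% and 78% banded against 34%, 73% and 91% continuous. The typical loss is about 12–15 points.

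**5. The reverse case.** If the true effect is a step exactly at 18, the split is the better form by about 10–12 points (9–20 over a wider set of scenarios).

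**6. Age confounding.** Assumptions: no true treatment effect, age uniform from 4 to 40, and uptake and response both graded in age. The share of bias left is ln(OR banded) / ln(OR crude).

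| OR per SD of age | Crude OR | OR, age banded | OR, age continuous | Share left |
|---|---|---|---|---|
| 0.67 | 1.162 | 1.043 | 0.995 | 28% |
| 0.50 | 1.515 | 1.143 | 0.995 | 32% |
| 0.40 | 1.988 | 1.284 | 1.010 | 36% |

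On the risk-difference scale, standardised over the two bands, 0.010 of 0.036, 0.030 of 0.100 and 0.053 of 0.165 remain, or 28%, 30% and 32%.

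**7. CHAQ-DI: why not simply linear.** Assumed distribution: 3 × Beta(1.5, 2), rounded to 0.125. About 10% of the simulated scores fall exactly on 1 or 2. With a monotone effect of −1.0 log-odds per unit, power is 58% banded and 76% linear. A patient at 0 has no room to improve on the index, so response may be lower at both ends of the scale. With logit = 1.8 − k(DI − 1.4)², power is 22% banded against 10% linear (k = 1), 45% against 11% (k = 1.5) and 71% against 14% (k = 2). With a humped confounder, weighting on bands cuts a bias of 0.051 to 0.025, while a linear term leaves it at 0.051.

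**The case against.** Study size says that no formal hypothesis is tested, and the covariate models are secondary, so power carries limited weight. This stands in part, but lost information also widens intervals, and incomplete adjustment biases a comparison whether or not a test is run. The 18-year split also matches how the programme's earlier results were reported. That is a good reason to keep it in tables. It is not evidence of a step at 18.

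Some stronger readings are tempting, and the documents do not support them:

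- A reader might infer that all three covariates should be linear. For CHAQ-DI the gain depends on a monotone shape, and a plausible floor effect reverses it. For enzyme activity the bands lose little.
- A reader might set the band width of 1.0 against the GTR threshold for CHAQ-DI, "Improvement ≤ –0.130 [17"], and conclude that the bands are nearly eight times too wide. That threshold concerns change within a patient, not differences between patients at baseline. A floor on the index also does not rule out a response, because the quality-of-life domain has a pain endpoint as well and only two of three domains are needed.
- A reader might take the confounding figures as the bias of the plan as written. The article defines its score as the predicted probability of response, not of treatment, and names no weighting. The comparison is also conditional on enough untreated patients.
- A reader might call the regression the only analysis of who responds. Descriptive subgroup analyses are also allowed for.
- The absence of a rationale for the cut-points is not a fault in a condensed article.

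**Conclusion.** The point holds for age and for the CHAQ-DI notation. The coding is printed in the article, so it is a stated choice and not a detail left to an unseen analysis plan. If the age effect is graded, as the article's account of the disease suggests but does not prove, the split at 18 costs about 12–15 points of power at n = 70. It would leave roughly 30% of age confounding in a comparison that used a correctly defined treatment propensity score. A true step at 18 would favour the split by about 10–12 points. All of these sizes rest on assumed age distributions and effects.

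The CHAQ-DI overlap is certain on the text but small: it concerns only scores of exactly 1 or 2. The point does not extend to replacing the CHAQ-DI or enzyme-activity bands by linear terms.

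**What to change.** In Statistical analyses:

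- Enter age at treatment start (age at registry baseline for untreated patients) as a continuous term in the regression/logistic models and in the propensity model.
- Keep < 18 / ≥ 18 for descriptive tables and as a sensitivity analysis.
- Write the CHAQ-DI bands without overlap, for example 0 to < 1, 1 to < 2 and 2 to 3.
- Keep the bands as the main form for CHAQ-DI and residual enzymatic activity. A continuous form that allows curvature can serve as a sensitivity analysis.

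The cost is a change of wording. Age is already collected, and one continuous term uses the same single parameter as the two-level split. The small downside is an assumption of approximate linearity in age. The < 18 / ≥ 18 sensitivity analysis shows whether the conclusions depend on it. The definition of the propensity score as a probability of response is a separate matter that this change does not cure.
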